|-----------------------------------------------------------------------------------------|------------------------------------------------------------------------------------------------------------------------------------------------------------------------------------------------------------------------------------------------------------------------------------------------------------------------------------------------------------------------------------------------------------------------------------------------------------------------------------------------------------------------------------------------------------------------------------------------------------------------------------------------------------------------------------------------------------------------------------------------------------------------------------------------------------------------------------------------------------------------------------------------------------------------------------------------------------------------------------------------------------------------------------------------------------------------------------------------------------------------------------------------------------------------------------------------------|
| (during week 13)                                                                        | 
 
Review of dietary intake (collect diet history or review Easy Diet Diary tracking) and usual care blood glucose monitoring.
 
Discuss individual preferences, including any challenges or barriers to achieving the recommended carbohydrate target.
 
Carb target adjustment (opportunity 2): If appropriate, negotiate an adapted carbohydrate prescription (i.e., increase or decrease within 25-75 g/day) with the primary goal of achieving pre-specified blood glucose targets (4-6 mmol/L fasting, 4-8 mmol/L 2 hours post meal).
 
New meal plan provided, if applicable (25 g/day or 60 g/day sample meal plans).
 
Provide individualised dietary strategies for adhering to the intervention.
 
Review understanding of information provided in diet session 4.
 
Participants prompted to report any adverse events experienced (self-report) over previous 2 weeks (e.g., severe hypoglycaemia, digestive issues, low energy levels, headaches, etc.)
 
Participants encouraged to follow-up with their nominated healthcare professional to discuss insulin management.
 
      |
| Diet session 6
(start of week 16)                                             | 
 
Review of dietary intake (collect diet history or review Easy Diet Diary tracking) and usual care blood glucose monitoring.
 
Provide individualised dietary strategies for adhering to the intervention.
 
Participants prompted to report any adverse events experienced (self-report) over previous 2 weeks (e.g., severe hypoglycaemia, digestive issues, low energy levels, headaches, etc.)
 
Participants encouraged to follow-up with their nominated healthcare professional to discuss insulin management.
 
                                                                                                                                                                                                                                                                                                                                                                                                                                                                                                                                                                                                          |
| Clinic visit 5
(start of week 16)
Note – same day as diet session 6 | 
 
Equipment, demonstration and instructions provided for: 
 
CGM/FGM device (sensor(s) and reader) (7-day monitoring)
 
Insulin logbook (3-day monitoring)
 
Diet record (Easy Diet Diary mobile app) (3-day monitoring)
 
Biological samples (Australian Clinical Labs request form provided)
 
 
 
                                                                                                                                                                                                                                                                                                                                                                                                                                                                                                                                                                                                                                                                                                                                                                                  |
| Clinic visit 6
(end of week 16)                                               | 
 
Morning of clinic visit 6: Participants attend their nearest Australian Clinical Labs collection centre (fasted) to have biological samples taken. Participants instructed to have a meal and drink fluids after blood draw and before their clinic visit.
 
Data collected (post-intervention outcomes): 
 
Return/upload CGM/FGM device/data
 
Return/upload insulin logbook
 
Return/upload diet record
 
Anthropometric measurements taken (weight, height, waist circumference and blood pressure)
 
Questionnaires completed (quality of life, physical activity, diet satisfaction)
 
 
 
End of intervention period – participants thanked for being involved in study and encouraged to follow up with usual healthcare team for all matters.
 
Provide letter with instructions for follow-up period (Attachment 14)
 
Provide pre-paid pathology request form (from iMedical) for follow-up HbA1c
 
Follow-up session scheduled and participants informed they will receive an email with instructions 2 weeks prior.
 
 |
| Follow-up Period                                                                 |                                                                                                                                                                                                                                                                                                                                                                                                                                                                                                                                                                                                                                                                                                                                                                                                                                                                                                                                                                                                                                                                                                                                                                                                      |
| Visit/session                                                                    | Outline                                                                                                                                                                                                                                                                                                                                                                                                                                                                                                                                                                                                                                                                                                                                                                                                                                                                                                                                                                                                                                                                                                                                                                                       |

|                                             |                                                                                                                                                                                                                                                                                                                                                                                                                                                                                                                                                                                           |
|---------------------------------------------|-------------------------------------------------------------------------------------------------------------------------------------------------------------------------------------------------------------------------------------------------------------------------------------------------------------------------------------------------------------------------------------------------------------------------------------------------------------------------------------------------------------------------------------------------------------------------------------------|
| Email reminder
(start of week 27) | 
 
• Participants reminded that they will need to visit an Australian Clinical Labs pathology collection centre ~3 days before their follow-up session.
 
• Brief outline for follow-up call provided.
 
                                                                                                                                                                                                                                                                                                                              |
| Follow-up session (end of week 28)   | 
Telehealth call (Zoom) with study dietitian.
 
 
• Data collected (post-control/pre-intervention outcomes): 
 
- HbA1c (collected via Australian Clinical Labs and iMedical)
 
- Total daily insulin use (24-hour)
 
- Diet recall (24-hour)
 
- Questionnaires completed (quality of life, diet satisfaction)
 
 
 
• End of study – participants thanked for being involved in study and reminded to follow up with usual healthcare team for all matters.
 
 |

Text message reminders will be sent to participants the day before each visit/session.

[figure not shown]

Figure 1. Overview of Contact Schedule for Participants

Abbreviations: CGM, continuous glucose monitor; T1D, type 1 diabetes; HCP, healthcare practitioner; Ax, assessment; req., required; inc., including; d, day; ACL, Australian Clinical Labs Pathology Collection Centre.

Clinic visits may be completed online via Zoom video Conferencing or in person at the Susan Wakil Health Building at the University of Sydney .

Table 2. Study Milestones

| Milestone | Description                                                                                | Time      | Date                           |
|-----------|--------------------------------------------------------------------------------------------|-----------|--------------------------------|
| #1        | Study starts & recruitment period begins                                                   | 0 months  | 21 st June 2021     |
| #2        | Recruitment period ends (unless 20 participants recruited prior)                           | 5 months  | 30 th November 2021 |
| #3        | The last recruited participant completes intervention period* (if recruited on 30/11/21)   | 8 months  | 31 st March 2022    |
| #4        | The last recruited participant completes follow-up period (final point of data collection) | 12 months | 30 th June 2022     |
| #5        | Study ends                                                                                 | 12 months | 30 th June 2022     |

\*based on 18 weeks from completing REDCap survey to completing intervention period.

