| OBJECTIVES              | The aim of this research is to assess the efficacy of a low-carbohydrate (LC) diet in adults with type 1 diabetes (T1D). We will specifically set out to determine whether significant differences in T1D management outcomes exist between a LC diet and habitual diets higher in carbohydrate.                                                                                                                                                                                                                                                                                                                                                                                                  |
| PRIMARY HYPOTHESIS      | A low-carbohydrate (LC) diet will result in improved type 1 diabetes management compared to habitual diets higher in carbohydrates.                                                                                                                                                                                                                                                                                                                                                                                                                                                                                                                                                               |
| DESIGN                  | This is a 28-week single arm within-participant intervention study involving a 4-week control period, a 12-week intervention period and a 12-week follow-up.                                                                                                                                                                                                                                                                                                                                                                                                                                                                                                                                      |

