After all baseline data (for the control period) has been collected, [name] will provide participants with instructions for the next four weeks which is to maintain usual patterns of eating, exercise and T1D management (Attachment 24). However, participants will be required to test their blood glucose levels at least six times daily, in accordance with standard

diabetes management practices, using whatever method(s) they usually use to test glucose. The dietitian will provide instructions and written resources on blood glucose monitoring (Attachment 47), managing hypoglycaemia (Attachment 48) and managing sick days (Attachment 46) (Table 1). There will be a diet session (Diet Session 0) scheduled in after two weeks and some basic diet education on carbohydrate counting (Attachment 25) and reading food labels (Attachment 26) will be provided (Table 1). During the last week of the control period, all of the same health assessments described above will be repeated (Table 1 and Figure 1). On the last day of the control period (end of Week 4), participants will have their first diet session of the intervention period (Diet Session 1) with the study dietitian and the intervention period will commence.

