### 7.3.2 Hypoglycaemia

Hypoglycaemia is a common acute complication of T1D which generally results from the difficulties in predicting expected rises in blood glucoses levels and accurately calculating insulin requirements. Due to the expected change(s) in insulin requirements as a result of the diet intervention, there is a risk of participants miscalculating their insulin requirements in the early stage of the intervention which could lead to increased frequency and/or severity of hypoglycemia. This will be mitigated by close monitoring of blood glucose levels, regular contact with the study dietitian, ongoing support from a nominated HCP, and oversight/supervision by the study physician, study diabetes educator and study endocrinologist.

Hypoglycaemia is defined by Diabetes Australia as a blood glucose level below 4 mmol/L [27]. The resources developed by the study dietitian and diabetes educator titled 'Managing hypoglycaemia' (Attachments 42 and 48) provide participants with information and guidelines on preventing and/or managing hypoglycaemia during the study. Participants will be required to test their blood glucose levels at least six times every day (i.e., before and 2 hours after each meal) using their own glucose monitoring

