| Diet session 2
(during week 7)  | 
 
• Telehealth call (Zoom) with study dietitian.
 
• Review of dietary intake (collect diet history or review Easy Diet Diary tracking) and usual care blood glucose monitoring.
 
• Provide individualised dietary strategies for adhering to the intervention.
 
• Review understanding of information provided in diet session 1.
 
• Diet resources discussed in this session:               
 
- Dietary proteins
 
- Dietary fats
 
- Snack ideas
 
 
 
• Participants prompted to report any adverse events experienced (self-report) over previous 2 weeks (e.g., hypoglycaemia (<3.5 mmol/L), digestive issues, low energy levels, headaches, etc.)
 
• Participants encouraged to follow-up with their nominated healthcare professional to discuss insulin management.
 
                                                                                                                                                                                                                                                                                                                                          |

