| Diet session 4
(during week 11) | 
 
• Telehealth call (Zoom) with study dietitian.
 
• Review of dietary intake (collect diet history or review Easy Diet Diary tracking) and usual care blood glucose monitoring.
 
• Provide individualised dietary strategies for adhering to the intervention.
 
• Diet resources discussed in this session:               
 
- Fast food, takeaway & dining out
 
- Reading food labels
 
- Shopping & food traps
 
- Gut upset on low carb
 
 
 
• Data collected on any side effects experienced by participants (self-report) over previous 2 weeks (e.g., hypoglycaemia (<3.5 mmol/L), digestive issues, low energy levels, headaches, etc.)
 
• Participants encouraged to follow-up with their nominated healthcare professional to discuss insulin management.
 
                                                                                                                                                                                                                                                                                                                                           |

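### Table 1's adverse-event prompts look back two weeks, but its end intervals are longer and the last on-diet visit has no prompt, so about 14 of 84 diet days lie outside every scheduled look-back.

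*Protocol*

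**What the plan says.** The Synopsis sets "a 4-week control period, a 12-week intervention period and a 12-week follow-up". Section 6.5 fixes the start of the diet: "On the last day of the control period (end of Week 4), participants will have their first diet session of the intervention period".

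Table 1 (Section 15) then places diet session 2 during week 7, session 3 during week 9, session 4 during week 11, session 5 "during week 13" and session 6 at the "start of week 16". At sessions 2, 3, 5 and 6 the entry is "Participants prompted to report any adverse events experienced (self-report) over previous 2 weeks". Session 4 words it as "Data collected on any side effects experienced by participants (self-report) over previous 2 weeks". Both forms carry the same two-week limit.

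The entry for clinic visit 6 (end of week 16) lists data collection and a closing step, with "participants thanked for being involved in study and encouraged to follow up with usual healthcare team for all matters", but no adverse-event enquiry. The diabetes education session (week 5 or 6) and the week-28 follow-up session list none either.

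Elsewhere the sessions are described as fortnightly: in the Synopsis (Intervention), in Section 6.6.4 and in Section 7.3.3. Section 8.1 and Table 1 also ask participants to report adverse events on their own initiative; Section 8.1 limits this to the control and intervention periods.

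**The concern.** A two-week look-back is complete only if the enquiries are at most two weeks apart and one falls at the end of the period. The fortnightly description in the body text would meet the first condition. The calendar in Table 1 does not meet it at either end of the diet, and the second condition fails because the last prompt comes at the start of the last week.

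An event in an uncovered day enters the solicited record only if the participant volunteers it or the dietitian asks more widely than the wording requires. With a single arm there is no comparison group in which the same omission would occur, so missed events lower the reported on-diet frequency directly. Section 7.3.2 says that "there is a risk of participants miscalculating their insulin requirements in the early stage of the intervention", which is why a possible gap at the start of the diet draws attention.

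**Working it through.** **Inputs (all from the protocol).** Intervention 12 weeks (Synopsis); diet session 1 on the last day of week 4 (Section 6.5, Table 1); session weeks and the two-week look-back (Table 1).

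**Calendar.** Call the last day of week 4 day 0. Week w then covers days 7(w − 5) + 1 to 7(w − 5) + 7. Week 16 ends on day 7 × 11 + 7 = 84, which reproduces the stated 12 weeks (84 / 7 = 12).

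| Contact | Diet day | Prompt |
|---|---|---|
| Session 1 | 0 | diet starts |
| Session 2 (week 7) | 15–21 | 2 weeks |
| Session 3 (week 9) | 29–35 | 2 weeks |
| Session 4 (week 11) | 43–49 | 2 weeks |
| Session 5 (week 13) | 57–63 | 2 weeks |
| Session 6 (start of week 16) | 78 | 2 weeks |
| Clinic visit 6 (end of week 16) | 84 | none |

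**Intervals.** Session 1 to 2: 15 − 0 = 15 up to 21 − 0 = 21 days. Session 5 to 6: 78 − 63 = 15 up to 78 − 57 = 21 days. Both always exceed 14.

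**Upper limit on coverage.** 5 prompts × 14 days = 70 days, so at least 84 − 70 = 14 days (16.7%) are uncovered.

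**Where the holes fall.** Let a prompt on day d cover days d − 14 to d − 1, and let s2 and s5 be the days of sessions 2 and 5.
- Start of diet: s2 − 15, which is 0 to 6 days.
- Before session 6, whose look-back begins on day 64: 64 − s5, which is 1 to 7 days.
- From session 6 onward: days 78 to 84, which is 7 days.

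With sessions 2 to 5 exactly 14 days apart, s5 = s2 + 42, and the total is (s2 − 15) + (64 − s2 − 42) + 7 = 14 whatever the weekday. Counting the session day in the 14 (d − 13 to d) moves one day from the end to the start and leaves the total at 14.

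**Weekdays free within the stated weeks.** All 7 × 7 × 7 × 7 = 2,401 combinations give 14 to 26 uncovered days, mean 17.4. The maximum, sessions on days 21, 29, 49, 57 and 78, leaves days 1–6, 29–34, 57–63 and 78–84 uncovered: 6 + 6 + 7 + 7 = 26 (31%).

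**A more generous reading.** If the look-back is 15 inclusive days (d − 14 to d), coverage is at most 5 × 15 = 75 days, so at least 84 − 75 = 9 days (10.7%) are uncovered. This minimum needs sessions 2 to 5 to be 15 days apart (days 15, 30, 45, 60). At 14-day spacing the figure is (s2 − 15) + (63 − s2 − 42) + 6 = 12. The maximum is 23.

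**Effect of a change.** Adding only a two-week prompt at clinic visit 6 still leaves 8 to 20 days uncovered. Asking since the previous enquiry and adding the prompt at clinic visit 6 leaves 0.

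**The case against.** The strongest reply is that the prompt is not the main safety net.
- **Glucose.** Section 7.3.2 requires at least six tests a day, fortnightly review by the dietitian and flagging of repeated low readings. Referred cases count toward the safety assessment.
- **Ketones.** Sections 6.6.3 and 7.3.4 require immediate reporting above a stated level.
- **Salt-related symptoms.** Section 7.3.3 has headache, low energy and constipation, among others, checked at each diet session with no look-back limit.
- **Week 16.** The 7-day glucose sensor runs through this week, and bloods at clinic visit 6 include sodium.
- **Early weeks.** Table 1 has a diabetes education session in week 5 or 6, and participants are encouraged to see their nominated practitioner within 7 days of diet session 1.

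All of this stands, and it narrows the point to solicited events that these routes do not reach. The salt-symptom check belongs to diet sessions, so it does not extend past session 6 either.

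A second reply is that two weeks is shorthand for the time since the last session, and that a participant would hardly omit an event because it happened 16 days ago. That may describe practice, but the written prompt does not say so, and under any reading there is no enquiry after session 6.

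A reader might infer that these days are never asked about at all, or that harm is undercounted exactly where it is most expected. The documents support neither. The other routes cover the early risk that Section 7.3.2 names, which is hypoglycaemia, and the hole at the start is 0 days if session 2 falls on the first day of week 7. Nor is 14 a strict minimum, since the protocol does not define the look-back to the day.

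**Conclusion.** The point holds as a mismatch within the protocol: a two-week look-back, sessions described as fortnightly, and a Table 1 calendar with 15 to 21 days at each end and no prompt at the last on-diet visit. About 14 of 84 diet days fall outside every scheduled look-back; the range is 9 to 26 according to day counting and weekdays. The holes are 0 to 6 days at the start, up to 7 days before session 6, and in every case about the final week.

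This assumes that the look-back is applied as written, that sessions fall in their stated weeks with session 6 on the first day of week 16, and that session 4's side-effect wording is equivalent to the other prompts. If it is not, more days are uncovered.

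The consequence is limited. The exposure is mainly solicited non-glycaemic events, such as digestive upset, and not all safety signals. Section 9 does not list adverse-event frequency as an outcome, so no primary or secondary result changes. It is worth correcting because the gap is built into the schedule and is cheap to close.

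**What to change.** In Table 1, at diet sessions 2 to 6, replace the two-week limit with a request for all events since the last adverse-event enquiry (or since diet start, at session 2). Naming the enquiry avoids the clock being reset by the education session, which has no prompt. Use the same wording at session 4. Add the prompt at clinic visit 6, and record a start date for each event. Both parts are needed, as the 8 to 20 days left by a visit-6 prompt alone show.

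The cost is one wording change in Table 1 and the REDCap form, and about two minutes at a visit that already takes place. The small downside is that recall stretches to as much as about three weeks at sessions 2 and 6.
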